## Abstract

**Background:**

Neuropathic pain (NP) is characterized as pain arising from lesions of the somatosensory nervous system. However, NP-like features have been found in several chronic secondary musculoskeletal (MSK) pain conditions in the absence of detectable lesion or damage to the somatosensory pathways. Emerging evidence has demonstrated associations between NP-like symptoms and altered neural activity within brain regions implicated in sensory perception and affective-emotional processing of pain with consistent findings of abnormal activity in the right insula (RIns) cortex and dorsal anterior cingulate cortex (dACC). Electroencephalography neurofeedback (EEG-NF) is a brain-computer interface biofeedback technique that allows individuals to self-regulate the real-time cortical brain activities of the regions of interest.

**Objective:**

The primary objective of this study is to investigate the feasibility and safety of a novel EEG-NF intervention designed to simultaneously downtrain activity in the RIns and dACC in individuals with a chronic secondary MSK pain condition exhibiting NP-like features. In addition, this study will conduct secondary exploratory analyses to investigate EEG-derived neuronal changes and their associations with clinical and experimental pain outcomes following the EEG-NF training.

**Methods:**

We will design a single-arm, open-label, pilot-feasibility trial. We will recruit adults aged 35-75 years with a score of ≥19 using the PainDETECT questionnaire and an average pain score of ≥4 on the 11-point Numeric Pain Rating Scale over the last 3 months, with a minimum pain duration of 3 months, to receive active EEG-NF training. Participants will receive auditory feedback as a reward for achieving a predetermined activity threshold of the RIns and dACC. Primary outcomes will evaluate feasibility, acceptability, and safety using both self-reported questionnaires and monitoring data. Collected data will be summarized descriptively, with mean (SD) reported where appropriate. Secondary outcomes will include EEG parameters, self-reported measures, heart rate variability, and quantitative sensory testing. An exploratory within-group pre-post statistical comparison will be conducted for all secondary outcome measures, and correlation analysis will be performed to explore relationships between EEG measures, self-reported outcomes, heart rate variability, and quantitative sensory testing measures.

**Results:**

This study has received approval from the Health and Disability Ethics Committee and is registered with the Australian New Zealand Clinical Trials Registry. Participant recruitment began in April 2025 and is ongoing. As of October 2025, data collection has been completed, with a total of 5 participants enrolled, all of whom have completed the study to date. We expect to complete the study in March 2026. This study will generate data on feasibility, safety, acceptability, and preliminary data to inform a fully powered effectiveness clinical trial.

**Conclusions:**

The results and data generated will inform the design and sample size calculation for a fully powered randomized controlled trial aimed at evaluating the effectiveness of EEG-NF in targeting NP-like features in individuals with chronic MSK pain.

**Trial Registration:**

Australian New Zealand Clinical Trials Registry ACTRN12625000706471; https://www.anzctr.org.au/Trial/Registration/TrialReview.aspx?id=389568&isReview=true

**International Registered Report Identifier (IRRID):**

DERR1-10.2196/78806

## Introduction

Chronic musculoskeletal (MSK) pain is the leading cause of disability, affecting over 1.7 billion people globally [1]. In New Zealand, one-quarter of the population is affected by some form of MSK disorder, and one-fifth of the population lives with chronic pain [2,3]. A subgroup of chronic MSK pain exhibits neuropathic pain (NP)-like qualities, which include symptoms such as burning, shocking, shooting, numbness, and “pins and needles” [4-8]. According to the International Association for the Study of Pain, NP is caused by a lesion or disease affecting the somatosensory system and may involve either the central or peripheral nervous system [9,10]. However, chronic secondary MSK conditions, such as knee osteoarthritis, low back pain, shoulder pain, neck pain, and osteoporosis, have been reported to exhibit NP-like qualities with widespread pain localization in 5.4%-33% cases in the absence of a verifiable lesion affecting the somatosensory system [4,8,11-14]. Similar findings have been observed in chronic widespread pain conditions, like fibromyalgia, which exhibit NP-like symptoms despite the absence of direct somatosensory lesions [15,16]. Moreover, patients with chronic MSK pain experience higher degrees of pain unpleasantness and bothersomeness, leading to emotional distress, which are part of the affective dimensions of pain [17,18]. Concurrently, the severity of symptoms or pain intensity may not always correlate to the extent of the MSK injury in these individuals [19,20].

Persistent pain associated with chronic MSK conditions and ongoing nociceptive input may lead to sensitization and widespread pain distribution, accompanied by altered sensory perception and changes in central processing within supraspinal structures [8,21]. Neuroimaging studies show that chronic MSK pain is associated with significant functional aberrations in brain regions involved in sensory processing, emotion and motivation, and pain inhibition [22,23]. Clinical aspects of pain correlate with these distinct anatomical brain regions and networks, as supported by functional neuroimaging data [24]. In particular, the insular cortex, specifically right insula (RIns) cortex and dorsal anterior cingulate cortex (dACC), plays a profound role in the sensory perception and emotional processing of pain and has been shown to exhibit alterations in chronic MSK pain conditions [25,26].

The insular cortex acts as a hub for cortical processing, including sensory, emotional, social, and cognitive information [27]. In particular, the insula serves as a hub linking multiple networks, including regions involved in pain mediation, such as the salience and ventral frontoparietal attention networks [28,29]. It has been shown that pain experience is associated with salience network, with the insular cortex serving as a key hub. The insular cortex is lateralized in function, with the RIns being predominantly involved in pain perception compared with the left insula [25]. Increased activation of the RIns has been reported in individuals with chronic MSK pain in both functional magnetic resonance imaging studies and electroencephalogram (EEG) studies in the gamma frequency band [30-32]. The insular cortex is also involved in modulating pain intensity, as it has been linked to pain catastrophizing [27,33]. Studies suggest that both the insula and the dACC are involved in the emotional processing of pain [34-37]. The dACC is the main proxy for the medial suffering pain pathway and is associated with motivational-affective component of pain [38]. Alterations in the activity of the dACC, such as increased activity in the alpha and beta frequencies and decreased functional connectivity to other regions, including the pregenual anterior cingulate cortex and somatosensory cortex, have been shown in people with chronic NP [38-40]. Previous studies have demonstrated that NP-like symptoms in individuals with painful knee osteoarthritis are associated with altered infraslow frequency (ISF) activity in the RIns and dACC, with significant correlations observed between ISF fluctuations and pain measures [30,41-44]. Therefore, targeting the ISF activity of both the RIns and dACC, which are associated with sensory and affective dimensions of pain, may modulate NP-like symptoms and produce clinical improvements in individuals with chronic MSK pain [26,27,38].

Currently, pharmacological treatments for NP conditions produce modest efficacy, potentially due to the variation in underlying mechanisms [45]. Furthermore, many available nonpharmacological treatments for NP conditions have demonstrated either low certainty of evidence or inconclusive results, highlighting the need for novel, innovative interventions [45,46]. Electroencephalography neurofeedback (EEG-NF) is a brain-computer interface biofeedback technique that allows individuals to self-regulate the real-time cortical brain activities of the regions of interest and reinforces learning using operant conditioning [47,48]. EEG-NF has been used successfully in several conditions, including chronic MSK pain, demonstrating clinical and EEG modulation [49-52]. EEG-NF training, which targets the ISF band in the brain, has been shown to provide clinical benefits [41,52]. Moreover, the ISF band has been shown to modulate higher-frequency brain oscillations through phase-locking mechanisms [53]. Previous studies have demonstrated that ISF EEG-NF training can influence resting-state brain networks and oscillations in various conditions, including targeting the dACC for chronic MSK pain [43,49,50,52,54,55]. However, to date, no studies have investigated the potential of ISF EEG-NF training for NP-like qualities in chronic MSK conditions. Furthermore, no research has explored the use of neurofeedback to simultaneously downtrain 2 distinct brain regions (dACC and RIns) as a targeted intervention for chronic MSK pain. This dual-target approach and ISF modulation for NP management highlight a novel strategy with the potential to achieve more comprehensive modulation of pain-related neural networks and clinical pain improvements.

Therefore, this study aims, for the first time, to explore the potential of downregulating the ISF activity of both the RIns and dACC using a novel ISF EEG-NF protocol in individuals with NP-like symptoms associated with chronic MSK pain conditions. Given the novelty of the proposed ISF EEG-NF training protocol, pilot testing of the protocol and assessment of feasibility and safety are necessary. The primary objectives of this study are (1) to pilot test and investigate the feasibility of the EEG-NF program, and (2) to investigate the safety of the ISF EEG-NF training. The secondary objectives are (1) to estimate the variability of the outcome measures for informing the sample size of a fully powered clinical trial, (2) to explore the immediate and short-term trends of the effects of the targeted ISF EEG-NF training on pain measures, and (3) to explore the changes in EEG current density activity at the targeted cortical regions (dACC and RIns) and the functional connectivity between these regions following ISF EEG-NF training.

## Methods

### Ethical Considerations

We obtained Ethical approval from the Health & Disability Ethics Committee, New Zealand (Reference 2023 EXP 19190). Research consultation with Māori was obtained from the Ngāi Tahu Research Consultation Committee (Reference 24402). The trial has been prospectively registered in the Australian New Zealand Clinical Trials Registry (ACTRN12625000706471).

All eligible participants will receive an information sheet with consent form outlining the study design and purpose. Participants who are enrolled will complete a digital consent form on the day before their baseline assessment and provide a signed paper copy upon attending in person. Participants may opt-out at any point during the study. All data for primary and secondary outcomes will be deidentified before analysis. In recognition of their time and contribution to the research, participants will receive NZ $200 (US $115) supermarket vouchers upon completion of all study sessions.

### Study Design

A single-arm, open-label, pilot-feasibility clinical trial was designed according to the Standard Protocol Items: Recommendations for Interventional Trials (SPIRIT; Multimedia Appendix 1) and the Consolidated Standards of Reporting Trials (CONSORT; Multimedia Appendix 2) extension for pilot and feasibility trials. The trial will be conducted in Dunedin, New Zealand, and the study phases are summarized in Figure 1 [56,57]. This study was designed as an open-label trial to assess the feasibility, acceptability, safety, and preliminary data of the developed EEG-NF training. Given the pilot-feasibility design and exploratory nature of the study, inclusion of a control group was not necessary at this stage. The primary focus is to gather preliminary data on EEG-NF training implementation and variability in clinical outcomes, which will inform a future fully powered clinical trial [58-60]. A structured description of the intervention is summarized in Multimedia Appendix 3, following the Template for Intervention Description and Replication (TiDiR) guide (Multimedia Appendix 3) [61].

**Figure 1 figure1:**
[figure not shown]
Diagram of participant flow for the study. NF: neurofeedback.

### Recruitment

Convenience sampling will be used to recruit participants from the wider Dunedin community. Periodic advertising in community newspapers and social media will be carried out. Posters will be placed throughout the local community to advertise the study for participant recruitment.

Interested participants will undergo eligibility screening by telephone or through a secure online survey using Research Electronic Data Capture (REDCap; Vanderbilt University) web application [62]. As this is a pilot-feasibility study, a formal power-based sample size calculation was not undertaken. Instead, the sample size was determined as 6-12 participants over a 4-month recruitment period, in accordance with recommendations for feasibility studies and previous literature, ensuring adequacy to evaluate safety and feasibility outcomes while also permitting exploratory analyses [63].

### Eligibility Criteria

Participants aged 35-75 years with MSK pain, averaging a score of ≥4 on the 11-point Numeric Pain Rating Scale over the past 3 months, with a minimum pain duration of 3 months, and a score of at least 19 on the PainDETECT questionnaire will be eligible to participate in this study [6,14,64-67].

Participants will be excluded if they have one of the following conditions or situations**:** systemic rheumatic conditions, neurological conditions, major psychiatric illness, cervical or lumbar radiculopathy, peripheral entrapment neuropathies, cognitive impairment, have undergone any surgery or intra-articular steroid injections in the 3 months before the study, have undergone any intra-articular hyaluronic acid injections in the 6 months before the study, are scheduled to undergo any surgery within 6 months of enrollment in the study, have undergone previous neurological procedures of the brain, are pregnant or up to 6 months postpartum, cardiovascular disease, peripheral arterial disease of limbs, uncontrolled hypertension (≥150/95 mm Hg), or uncontrolled diabetes.

### Screening and Enrollment

Interested participants will undergo a brief preliminary screening for initial eligibility by telephone or through an online questionnaire using the REDCap online survey platform [68]. If the initial eligibility criteria are satisfied, participants will undergo a detailed screening based on their health information through a secure online survey. Participants will then be given an appointment for the final confirmatory screening.

A paper-based Montreal Cognitive Assessment will be carried out to screen for cognitive impairments [69]. The maximum Montreal Cognitive Assessment score is 30 points, and only those who score 21 or above will be eligible to participate in this study, based on normative data for the population included in the study [69,70]. If the participant meets this threshold and is found to be eligible, baseline assessment will continue.

Eligible participants will undergo 12 sessions (30 minutes each; 3 sessions per week) of ISF EEG-NF training and two 90-minute baseline and postintervention assessments at the Department of Anatomy–Research Clinic facility at the University of Otago, New Zealand. The intervention will be provided by a researcher experienced in the delivery of neurofeedback. Participants will be required to abstain from alcohol and caffeinated beverages for 24 hours and from food and drinks for at least 1 hour before any assessment sessions [71].

### Intervention: ISF EEG-NF Training

At the start of each session, participants will be seated in a chair with back support and asked to remain relaxed for 10 minutes while the trainer prepares them for neurofeedback training. The ISF EEG-NF training will be administered using a 21-channel DC-coupled amplifier (BrainMaster Technologies Inc) with a Comby EEG lead cap containing Ag/AgCl sensors of an appropriate size, secured to the participant’s head. Reference electrodes will be placed at the mastoids [72]. The impedance of the active electrodes will be continuously monitored to remain below 5 kΩ [49,52,72]. Participants will be advised to minimize eyeball, head, and neck movements, swallowing, and clenching of teeth to reduce motion artifacts in the EEG data [73]. Treatment adherence will be ensured by directly observing participants throughout the training sessions.

Participants will be instructed to relax, keep their eyes closed, and listen to the audio feedback. For this study, an ISF EEG-NF program to downtrain the RIns and dACC was developed using the BrainAvatar Live standardized low-resolution electromagnetic brain tomography projector software [52,74]. Standardized low-resolution electromagnetic brain tomography allows the selection of brain regions (region of interest [ROI]) for EEG-NF training based on the current density of the ROI and 3D brain mapping functionality [74-76]. A visual representation of the ROIs, direction of training, and an overview of outcome measures are provided in Figure 2. The figure was generated using BrainNet Viewer [77] and BioRender [78].

**Figure 2 figure2:**
[figure not shown]
Regions of interest and outcome measures. dACC: dorsal anterior cingulate cortex; ECG: electrocardiogram; EEG-NF: electroencephalography neurofeedback; ISF: infraslow frequency; QST: quantitative sensory testing; RIns: right insula; ROI: region of interest.

The BrainMaster Technologies software (BrainAvatar) will deliver real-time auditory feedback when participants’ brain activity is simultaneously downregulated within the ROIs—the dACC and RIns—in the ISF (0.0-0.1 Hz) band. The BrainAvatar auditory feedback is generated using Musical Instrument Digital Interface–based tones and sound effects. The auditory feedback serves as a primary reinforcement modality, providing immediate and intuitive cues that reflect real-time brain activity. The system incorporates a range of sounds, including simple tones, chimes, and naturalistic effects such as chirps or gongs, which vary in pitch, clarity, or occurrence depending on whether the individual’s brainwave activity meets the targeted thresholds. For example, reward tones or sound effects are triggered only when the desired neural patterns are achieved, whereas the absence, distortion, or reduction of sound indicates deviation from the training goals. This dynamic modulation allows the brain to receive continuous, nonverbal information about its own functioning, supporting operant conditioning and the self-regulation processes central to effective neurofeedback training [47,48].

The auditory feedback (reward) will be captured using Audacity, a free and open-source audio recording and editing software [79]. Audacity can use the computer’s microphone and sound card as its own audio-to-digital converter, eliminating the need for additional equipment. The auditory feedback will then be used to calculate the duration of successful neurofeedback training, defined as the cumulative time that the participant received the auditory reward feedback during the 30-minute neurofeedback session [80]. The duration of successful neurofeedback training from each participant across the 12 sessions will be included in the analysis.

The target ROIs were chosen based on previous literature related to EEG-NF and MSK pain conditions [30,31,50,52]. The reward threshold will be continuously monitored by the trainer and adjusted manually if cortical activity falls outside the desired threshold [49,52,72]. The duration and number of neurofeedback sessions were informed by recent studies using ISF EEG-NF for chronic pain management, which demonstrated changes in clinical pain outcomes, and were selected to ensure methodological rigor in this study [72,81].

### Baseline Assessment

Once written informed consent is obtained, participants will complete questionnaires that include demographics and general health information, such as age, sex, and ethnicity. Assessment of resting-state EEG and clinical and experimental pain outcomes will be conducted by a researcher who is adequately trained in all procedures.

### Primary Outcomes

The primary outcomes of this study will be the feasibility and safety measures [82]. These will be collected by the investigator throughout the study period, from recruitment until the last postintervention assessment session. Feasibility outcomes include the recruitment rate, defined as the number of participants attending a screening assessment each month; the enrollment rate, defined as the proportion of participants recruited from the total screened; the compliance rate, defined as the number of sessions attended by each participant out of the total sessions; and the dropout rate, defined as the number of participants who dropped out over course of the study [83,84]. All measures will be monitored through monthly audits of recruitment records during the first 4 months of the recruitment and intervention period.

An adverse event is defined as any harmful event or symptom from the trial that could reasonably be linked to the procedure or EEG-NF training. EEG-NF is a safe technique; however, all participants will be asked about any adverse events experienced from the previous session at each visit, and any worsened side effects compared with previous training will be recorded. All participants will be instructed to complete the Discontinuation Emergent Sign and Symptom scale [85], a 43-item checklist consisting of emotional, behavioral, cognitive, and physical symptoms. These symptoms can be considered possible side effects from neurofeedback training and have been used in previous literature as a measure of safety monitoring for similar studies [52,72].

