### Analysis

#### Primary Outcomes

Participant demographics, feasibility, acceptability, credibility, and safety data over the course of the study will be summarized descriptively [142]. Mean (SD) or median (IQR) when distributional assumptions are not met and CI (75% and 95%) of the clinical and quantitative outcome measures for the participants will be derived using GraphPad Prism software [143]. Feasibility will be assessed against prespecified progression criteria: ≥50% of eligible participants consenting, recruitment meeting target within the planned window (~6 participants in 4 months), retention ≥80% at postintervention, adherence ≥75% of scheduled sessions, data completeness ≥85%, and mean acceptability ≥70%. Each metric will be reported as a point estimate with 95% CIs, and progression will be discussed in light of these thresholds [60,144,145].

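### The adverse event definition requires a possible link to the trial procedures, with no stated rule or assessor, so the primary safety count may understate all-cause harm

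*Protocol article*

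**What the plan says.** The Introduction gives two primary objectives, and the second is "to investigate the safety of the ISF EEG-NF training". The Primary Outcomes section under Methods confirms that status: "The primary outcomes of this study will be the feasibility and safety measures". It then sets out how safety is measured:

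- **Definition.** An adverse event is "any harmful event or symptom from the trial that could reasonably be linked to the procedure or EEG-NF training".
- **Who collects.** "These will be collected by the investigator throughout the study period, from recruitment until the last postintervention assessment session". Nobody is named as judging whether a link is reasonable, and no criteria for that judgment are given.
- **Questioning.** "all participants will be asked about any adverse events experienced from the previous session at each visit".
- **Worsening.** "any worsened side effects compared with previous training will be recorded".
- **Checklist.** All participants complete a 43-item scale of emotional, behavioral, cognitive and physical symptoms. No attribution step is attached to it. The text does not say how its results enter the safety outcome, or against what reference they are read.

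The same paragraph describes the technique as safe before any data are presented. The Study Design section makes the trial single-arm and open-label. The Analysis section says that safety data will be summarized descriptively.

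**The concern.** The usual order is to record every untoward event and then to classify it by relatedness, severity and seriousness. Here the relatedness judgment comes first. An event thought unlinked is not an adverse event under the definition and need not be written down as one, so nobody can reassess it later.

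Three features of the trial make this matter. The simultaneous downtraining of two regions is described as new, so little prior experience is available to guide a judgment of what can be linked to it. There is no control arm, so no comparator rate can show whether events set aside as unlinked occur in excess. Participants have chronic pain, and many symptoms on the checklist are easily put down to the underlying condition.

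A second, smaller weakness is the reference point for worsening. Comparing each session with the one before detects a jump, but may not detect a slow drift across the 12 sessions.

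At stake is half of the primary question. A low or zero adverse event count would be carried into the case for a fully powered trial, although it describes only events that passed an unspecified filter.

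**Working it through.** **Inputs from the protocol article.** Planned sample size 6 to 12 (Recruitment); 5 enrolled as of October 2025 (Results); 12 training sessions (Screening and Enrollment). No safety rate, threshold or power is stated, so there is no figure of the plan's own to reproduce.

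**Inputs that are assumptions.** Let p be the per-participant risk of any untoward event, and s the share of such events thought linked and so counted. The documents give neither, so a range is shown.

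**Step 1: direction.** The counted rate is p × s, with s at most 1. Against an all-cause count, a relatedness condition can remove events but cannot add any.

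**Step 2: chance of counting no adverse events in n participants.** The formula is (1 − p × s)^n.

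With p = 0.30 and every event recorded (s = 1):
- n = 5: 0.70^5 = 0.168
- n = 6: 0.70^6 = 0.118
- n = 12: 0.70^12 = 0.014

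With p = 0.30 and half thought linked (s = 0.5), the counted rate is 0.15:
- n = 5: 0.85^5 = 0.444
- n = 6: 0.85^6 = 0.377
- n = 12: 0.85^12 = 0.142

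Over a wider range:

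| p | s | n = 5 | n = 6 | n = 12 |
|---|---|---|---|---|
| 0.10 | 1 | 0.590 | 0.531 | 0.282 |
| 0.10 | 0.5 | 0.774 | 0.735 | 0.540 |
| 0.10 | 0.25 | 0.881 | 0.859 | 0.738 |
| 0.30 | 1 | 0.168 | 0.118 | 0.014 |
| 0.30 | 0.5 | 0.444 | 0.377 | 0.142 |
| 0.30 | 0.25 | 0.677 | 0.626 | 0.392 |
| 0.50 | 1 | 0.031 | 0.016 | <0.001 |
| 0.50 | 0.5 | 0.237 | 0.178 | 0.032 |
| 0.50 | 0.25 | 0.513 | 0.449 | 0.201 |

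These figures concern the adverse event count alone and give the checklist no weight.

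**Step 3: what a zero count would show.** With 0 of n, the exact upper 95% limit is 1 − 0.05^(1/n) one-sided and 1 − 0.025^(1/n) two-sided.

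| n | one-sided | two-sided |
|---|---|---|
| 5 | 45.1% | 52.2% |
| 6 | 39.3% | 45.9% |
| 12 | 22.1% | 26.5% |

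Wide as they are, these limits bound only the risk of events that meet the definition. They say nothing about events set aside as unlinked.

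**Step 4: the reference for worsening.** Twelve sessions give 11 session-to-session comparisons. A symptom that rises by a small amount d at each one has risen by 11d from the first session to the last, yet no single comparison shows more than d. If d is too small to be reported as worse than last time, the rise is never recorded under that rule. A comparison with T1 would show it.

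**The case against.** The best defence is that the adverse event count is not the only safety measure. The checklist goes to all participants with no stated attribution step, and every visit includes active questioning. Pain severity, interference, unpleasantness, bothersomeness and mood are rated around the training sessions, and medication changes are noted at each one. Deterioration thought unlinked is therefore not simply lost. This stands, and it rules out saying that the safety outcome rests solely on attributed events. It does not remove the concern: the checklist's part in the safety outcome is not stated, the other ratings are not adverse event counts, and the question at each visit is framed in terms of adverse events and so carries the same condition.

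The wording also sets a low bar. It asks whether a link is reasonably possible, and it covers procedures as well as training, so it does not demand established causation. That limits the likely loss. Further, if the excluded events are truly unrelated, the count of training-related harm is not biased. Both points stand. They are why understatement of all-cause harm is possible but not shown.

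Several stronger readings are tempting, and the documents do not support them:

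- *An unblinded team filters the events.* With one arm there is no allocation to blind, and no assessor of relatedness is named. The gap is the missing rule.
- *A symptom that starts after session 1 and persists unchanged is lost.* The question at the next visit would elicit it if it meets the definition. The worsening rule is weak for gradual change only.
- *The trial may progress whatever harm is seen.* The Analysis section says "Feasibility will be assessed against prespecified progression criteria". That list has no safety item, but it is labelled as concerning feasibility, and progression is to be discussed against it. It is not an automatic go rule.
- *The checklist is not taken at baseline.* The article does not state its timing, and an article may leave that detail to the full protocol.

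**Conclusion.** The point holds as a defect in a stated rule. A primary outcome is defined through a relatedness judgment that has no stated criteria or assessor, in a design with no comparator, so the adverse event count may understate all-cause harm. The direction relative to an all-cause count is certain, since the condition can only remove events. The size cannot be computed from the documents. Over assumed risks of 10% to 50% and linked shares of 25% to 100%, the chance of counting no events runs from 0.031 to 0.881 with 5 participants, 0.016 to 0.859 with 6, and below 0.001 to 0.738 with 12. The 30% and 50% example is an illustration and not an estimate.

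The checklist offsets the loss in part, and how far depends on a role that the article leaves open. The session-to-session rule for worsening adds a lesser risk of missing slow deterioration. This should be fixed, but it does not invalidate the safety assessment.

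**What to change.** Define an adverse event as any untoward sign, symptom or event from consent (or from the first session) to T2, regardless of cause. Record relatedness, severity and seriousness as separate fields, and say who grades relatedness and by what rule. Report both all events and related events.

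State what part the 43-item checklist plays in the primary safety outcome. Report checklist symptoms that emerge or worsen relative to T1, or to the earliest checklist available, as well as from session to session.

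The Results section reports that data collection was complete with 5 participants, while the abstract also calls recruitment ongoing. For participants who have finished, a new definition cannot recover events that were never written down. For them, report every event and checklist symptom held on record, and state that events judged unlinked may not have been captured. The article already commits to documenting deviations in the registry and in the final publication, so the change has a place to be declared.

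The cost is a little more recording for any further participants, and an event count that may look less favourable.
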